### Oversight and Monitoring

The study will be overseen by the Trial Steering Committee (TSC) comprised of experienced chief investigators from the participating ICUs ([name], [name], [name], [name]), along with expertise in Infectious Diseases ([name]), Microbiology ([name], [name]), Bioinformatics ([name]) and Pharmacy ([name]). The TSC developed the protocol and meet monthly during the course of the trial. The TSC will evaluate any reports of adverse events (AEs), though few or no significant adverse events are anticipated in this study and a Data Safety and Monitoring Board (DSMB) was not convened. It is recognised that the patient population in the ICU will experience a number of aberrations in laboratory values, signs and symptoms due to the severity of the underlying disease and the impact of standard treatments in the ICU. These will not necessarily constitute AEs unless they are considered to be related to study treatment/procedures (ie. blood sampling and software-guided dosing) or in the Principal Investigator’s clinical judgement are not recognised events consistent with the patient’s underlying disease and expected clinical course. Therefore, reporting of AEs in this study will be restricted to events that occur during the study period (i.e., during and up to 48 hours after ceasing software-guided dosing), and which are considered to be related to study-specific procedures. Similarly, only serious adverse events (SAEs) that are reasonably suspected by the site principal investigator to be related to study-specific procedures and blood sample collection will be reported. Reporting of SAE in this study will be restricted to events that occur during the study period (i.e., during and up to 48 hours after ceasing software-guided dosing). SAEs will be reported to the steering committee within 24 hours of study staff becoming aware of the event. The SAE reports will then be forwarded to the HREC in accordance with local requirements. Patient eligibility, consents, and sample processing will be audited every 6 months at each site. An annual progress report will be submitted to the approving HREC & local RGOs. This process will be undertaken independently of the study sponsor. All protocol amendments will be agreed by the chief investigators, and submitted for ethical and local governance approval. Important protocol amendments will be updated on the published trials registry.

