**Participants and interventions:**

DIRECT will collect microbiological and pharmacokinetic samples from approximately 200 children and adults with sepsis admitted to one of four ICUs in Brisbane. In Phase 1, we will evaluate Oxford Nanopore Technologies MinION sequencing direct from blood in 50 blood culture-proven sepsis patients recruited from consecutive patients with suspected sepsis. In Phase 2, a further 50 consecutive patients with suspected sepsis will be recruited in whom MinION sequencing will be combined with Bayesian software-guided (ID-ODS) personalised antimicrobial dosing.

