### Data Collection and Management

Clinical data on patient demographics, comorbidities, type and focus of infection, severity, clinical progress through ICU and clinical outcomes (including ICU and hospital length of stay and in-hospital mortality) will be captured by clinical research nurses into an online REDCap database hosted by The University of Queensland. Organ dysfunction in children and adults is defined in **Supplementary File 2**. In the event that a paper Case report form is used, forms will be stored in an appropriate locked storage facility with restricted access. A study ID number will be used to link de-identified clinical data with the laboratory samples. Data and samples will be retained in line with the Queensland Health Retention and Disposal Schedule and with the Australian Code for the Responsible Conduct of Research Section 2.1.1. Deidentified genome sequence data will be shared by deposition in a public nucleotide repository (GenBank and Sequence Read Archive). Adherence to the study protocol will be monitored by the Coordinating Principal Investigator, and the steering committee. Patient eligibility, consents, and sample processing will be audited every 6 months at each site. An annual progress report will be submitted to the approving human research ethics committee (HREC) and local research governance officers (RGOs). No adverse events are anticipated, and a Data Safety and Monitoring Board has not been convened.

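### Adverse event reporting omits one limb of the protocol's own definition and leaves dosing-related serious events unclear, so a low count would say little about safety

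*Protocol article*

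**What the plan says.** All the safety wording is in the protocol article, under Oversight and Monitoring and under Data Collection and Management.

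- **Rationale.** ICU patients "will experience a number of aberrations in laboratory values, signs and symptoms due to the severity of the underlying disease" and because of standard ICU treatment, so such findings are not automatically adverse events.
- **Definition, limb one.** They do count if "considered to be related to study treatment/procedures (ie. blood sampling and software-guided dosing").
- **Definition, limb two.** Joined by an *or*: they also count if they, in the Principal Investigator's "clinical judgement are not recognised events consistent with the" patient's disease and expected course.
- **AE reporting rule.** The next sentence opens with *Therefore*. It restricts reporting to events in the study period, which closes 48 hours after guided dosing stops, "and which are considered to be related to study-specific procedures".
- **SAE reporting rule.** Only serious events "reasonably suspected by the site principal investigator to be related to study-specific procedures and blood sample collection will be reported".
- **Oversight.** "No adverse events are anticipated, and a Data Safety and Monitoring Board has not been convened". The steering committee reviews whatever is reported.
- **Other data.** Clinical progress, severity, ICU and hospital length of stay and in-hospital mortality are collected separately, with no attribution step. Organ dysfunction is defined in Supplementary File 2, which is not at hand.

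**The concern.** The reporting rule is presented as following from the definition, but it is narrower and no reason is given. A site that follows the text would record an unexpected, unattributed event as an adverse event and then not report it. That is the kind of event an attribution-based system most needs to catch, because early on nobody has a reason to suspect the intervention.

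The SAE sentence raises a second problem. Dosing is the part of the Phase 2 intervention that the definition names as treatment, yet it does not appear in the relatedness wording for serious events. Two sites could reasonably differ on whether a serious event suspected to come from dosing is reportable.

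The pilot is meant to inform later sepsis studies. If its safety message is a count of reported events, that count will reflect how events were attributed and how the sentences were read, as well as what guided dosing did.

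**Working it through.** No figure in the article bears on this point: it states no safety event rate, threshold or precision. The check is therefore a comparison of the sentences.

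**Step 1: definition against AE reporting rule.** Let R mean judged related and U mean judged not to fit the disease and expected course. The definition is R or U. The AE reporting rule is R, within the study period. Crossing the two judgements gives four classes:

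| Class | Related? | Fits the disease? | AE by definition? | Reportable? |
|---|---|---|---|---|
| A | yes | no | yes, both limbs | yes |
| B | yes | yes | yes, limb one | yes, if dosing counts as a study-specific procedure |
| C | no | no | yes, limb two | **no** |
| D | no | yes | not necessarily | no |

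Definition minus reporting rule is (R or U) without R, which is class C. That is the gap.

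**Step 2: what study-specific procedures covers.** Limb one speaks of treatment *and* procedures, and lists "ie. blood sampling and software-guided dosing". The AE reporting sentence drops the word treatment. The SAE sentence then places blood collection alongside study-specific procedures as a separate item. There are two readings:

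- The term carries limb one's meaning. Then blood sampling is already inside it, and naming it again is redundant.
- The term means something else. Then nothing in the sentence says that dosing is inside it.

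The reporting window is tied to the end of guided dosing, which favours including dosing. That is an inference, and the wording does not settle it. For AEs the article does not say who judges relatedness. For SAEs it names the site principal investigator.

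**Step 3: what a low count would mean.** With N participants exposed, a true rate r of dosing harm, and a probability a that such a harm is judged related, the expected number of reported harms is N × r × a. Here N = 50 (Sample Size and Recruitment). The article gives neither r nor a, and the count alone cannot separate them. A low count fits a small r, and it fits a small a equally well.

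**Step 4: whether Phase 1 supplies a reference count.** It does not. The window is defined by guided dosing, which belongs to Phase 2 (Figure 1 caption), so Phase 1 has no matching period for adverse events. Any side-by-side view has to use outcomes collected the same way in both phases. The article confirms in-hospital mortality and ICU and hospital length of stay as such outcomes.

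**The case against.** The case for leaving the text alone has real force. A reporting rule may be narrower than a definition, and in an ICU population some filter is needed to keep expected deterioration from swamping the reports. Limb one names dosing and the window is built around it. Every regimen is checked by the senior pharmacist and the attending consultant, and drug concentrations are measured. Mortality and length of stay are collected whatever anyone thinks caused them. The article is also a condensed account, so safety tables may exist in the full protocol or an analysis plan.

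Much of this stands, and it rules out two stronger readings.

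- A reader might infer that the reporting rule contradicts the definition. It does not. It is an unexplained narrowing, introduced by a *Therefore* that does not follow.
- A reader might infer that dosing toxicity resembling septic organ dysfunction cannot be seen because limb two was dropped. The text does not support this. Such toxicity fits the underlying disease, so limb two would exclude it as well (class D). If someone suspects dosing, it falls under limb one (class B). Deaths and length of stay are recorded in any case.

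The objection leaves three things unanswered: why class C events are not reported, whether dosing-related serious events are in scope, and how a count that depends wholly on attribution is to be interpreted. The first two are defects in wording that the article does state, so they cannot be put down to omitted detail.

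**Conclusion.** The point holds as a defect in stated rules. Class C events meet the definition and are not reportable, and the scope of SAE reporting for dosing is unclear. Independently of both, all reporting depends on attribution, with no randomised control and no data safety and monitoring board, so a low AE count would be weak evidence that guided dosing is safe.

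The size is not a number. It would need event rates and attribution probabilities that the article does not give, and any stated excess of harm among the 50 Phase 2 participants would rest on assumed rates.

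A reader might also infer that harm from a wrong sequencing result is improperly left out of the listed procedures, since in Phase 2 "MinION sequencing will be combined with Bayesian software-guided (ID-ODS) personalised antimicrobial dosing". The documents do not settle this. ONT MinION Nanopore Sequencing describes emulated real-time analysis of stored files, and Statistical Methods speaks of a projected time to optimal therapy. The omission matters only if sequencing results reach the treating team, which is a separate question.

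The conclusion assumes that the full protocol carries the same wording as the article. If it already reports both limbs and names dosing in both sentences, the wording part falls away.

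**What to change.** 1. **Reconcile the sentences.** Rewrite both reporting sentences so that events in the study period meeting either limb are reported. State that software-guided dosing is in scope for AEs and for SAEs, and use one term with one meaning throughout. If the narrower AE rule is intended, say so, give the reason, and remove the *Therefore*.
2. **Add one table that does not depend on attribution.** For all Phase 2 participants, show in-hospital mortality and ICU and hospital length of stay beside Phase 1, with 95% confidence intervals. Label it descriptive and non-randomised. Phase 2 enrols suspected sepsis, so the nearer comparison is with all of the approximately 150 Phase 1 recruits and not only the 50 with positive cultures. Add organ dysfunction only if it is already recorded during follow-up; the article says that it is defined, not that it is recorded serially.

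Cost: a wording amendment, somewhat more AE reports from limb two, and one table from data already collected. The table will be confounded by calendar time and cannot establish or exclude harm. Part 1 is needed even so, because the table does not recover class C events, and restoring limb two does not address toxicity that looks like sepsis.

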### Dissemination Plans

Results will be published in a peer-reviewed journal and presented at relevant conferences. A report will also be submitted to Queensland Health. All data will be non-identifiable and subgroup analyses will be presented in such a way as not to enable identification of participants and/or individual sites. Diagnostic accuracy will be reported in line with the Standards for Reporting of Diagnostic Accuracy Studies (STARD) statement (Bossuyt et al., 2015).

### Trial Status

Recruitment to the observational Phase 1 of the study commenced on 17th March 2020. Recruitment to the interventional Phase 2 commenced in March 2021 and recruitment is anticipated to finish on 30th September 2021.

## Discussion

Sepsis is a leading cause of preventable harm, and delays to appropriate antimicrobial therapy increase the risk of adverse outcomes. In critically ill patients, reducing the time to optimal therapy may yield significant improvements in sepsis mortality and ICU length of stay. Our innovative approach of combining rapid pathogen sequencing with antimicrobial dosing software has the potential to overcome the existing limitations of conventional diagnostics. Despite growing interest, and encouraging progress in the development of metagenomic sequencing for pathogen detection (Gu et al., 2021), there are few examples of its use in bloodstream infections or sepsis. A number of case studies ([name] et al., 2019), or small series (Grumaz et al., 2016; Grumaz et al., 2020) suggest the potential of the approach in this time-critical context. One other clinical trial is currently evaluating next generation sequencing in adults with sepsis (Brenner et al., 2018), but no published protocols which include children. Our pilot study will yield key feasibility data to inform further, urgently needed sepsis studies.

## Data Availability Statement

The raw data supporting the conclusions of this article will be made available by the authors, without undue reservation.

## Ethics Statement

The studies involving human participants were reviewed and approved by Children’s Health Queensland Hospital and Health Service Human Research Ethics Committee (HREC) [HREC/19/QCHQ/55177]. Written informed consent to participate in this study was provided by the participants’ legal guardian/next of kin.

